# Comparison of endoscopic ultrasound-guided hepaticogastrostomy and the antegrade technique in the management of unresectable malignant biliary obstruction: study protocol for a prospective, multicentre, randomised controlled trial

**DOI:** 10.1186/s13063-020-04758-5

**Published:** 2020-09-29

**Keywords:** Intrahepatic EUS-BD, Malignant biliary obstruction, EUS-HGS, EUS-AG, Randomised controlled trial

## Abstract

**Background:**

Endoscopic ultrasound-guided biliary drainage (EUS-BD) is used after failed endoscopic retrograde cholangiopancreatography. Based on existing studies, intrahepatic (IH) approaches are preferred in patients with dilated IH bile ducts. Both ultrasound-guided hepaticogastrostomy (EUS-HGS) and ultrasound-guided antegrade treatment (EUS-AG) are appropriate for patients with unreachable papillae. Nevertheless, there have been no direct comparisons between these two approaches. Therefore, we aim to evaluate and compare the safety and efficiency of EUS-HGS and EUS-AG in patients with an unreachable papilla.

**Methods:**

This is a prospective, randomised, controlled, multicentre study with two parallel groups without masking. One hundred forty-eight patients from three hospitals who met the inclusion criteria will be randomly assigned (1:1) to undergo either EUS-HGS or EUS-AG for relief of malignant biliary obstruction. The final study follow-up is scheduled at 1 year postoperatively. The primary endpoint is efficiency, described by technical and clinical success rates of EUS-HGS and EUS-AG in patients with unreachable papillae. The secondary endpoints include stent patency, overall survival rates, complication rates, length of hospital stays, and hospitalisation expenses. The chi-square test, Kaplan–Meier methods, log-rank test, and Cox regression analysis will be used to analyse the data.

**Discussion:**

To our knowledge, this is the first study to compare these two EUS-BD approaches directly using a multicentre, randomised, controlled trial design. The clinical economic indexes will also be compared, as they may also affect the patient’s choice. The result may contribute to establishing a strategic guideline for choosing IH EUS-BD approaches.

**Trial registration:**

Chinese Clinical Trial Registry (ChiCTR) ChiCTR1900020737. Registered on 15 January 2019

## Background

Obstructive jaundice is the main cause of death associated with malignant biliary tumours. However, because of its insidious onset, the detection of cholangiocarcinomas often occurs too late for surgical resection of the primary tumour. Endoscopic retrograde cholangiopancreatography (ERCP) has been the standard procedure for palliative biliary drainage in patients with both benign and malignant biliary obstructions [1]. Nevertheless, there remains a failure rate of ERCP because of the difficulty of cannulation occasioned by variations in ampullary anatomy [1–3]. The traditional way of relieving biliary obstruction after failed ERCP is percutaneous transhepatic biliary drainage. This long-term external drainage method can cause electrolyte imbalances, and the persistent pain and repeated infections associated with abdominal wall fistulas can severely affect the quality of life [3–6]. Therefore, since it was first described in 2001, ultrasound-guided biliary drainage (EUS-BD) has been increasingly used as an endoscopic alternative to failed ERCP because of its high success rate, low adverse event rate, and advantage of immediate internal drainage [7–9].

According to the drainage route, EUS-BD can be categorised into transduodenal extrahepatic approaches and transgastric intrahepatic (IH) approaches. With the advantage of a lower bile leakage rate and better retention of the original anatomical structure, the IH approaches are suggested to be the first choice for patients with a dilated IH bile duct after failed ERCP [10, 11]. IH approaches include the rendezvous technique (RV), ultrasound-guided hepaticogastrostomy (EUS-HGS), and ultrasound-guided antegrade treatment (EUS-AG). Because of the requirement of retrograde stent implantation, RV is not feasible for patients with inaccessible papillae, whereas hepaticogastrostomy (HGS) and the antegrade technique (AG) are [12, 13]. However, there is no consensus regarding options for biliary access [14, 15]. For patients with malignant biliary obstruction, it is a great challenge to tolerant procedures once and experience postoperative complications. Therefore, it is important to develop strategies for choosing among the approaches (EUS-HGS or EUS-AG) by comparing their safety and efficiency.

To date, several retrospective studies have compared EUS-HGS and EUS-AG; nevertheless, there has been no well-designed prospective, randomised study with robust data on this topic. Therefore, in the present study, we aim to compare the safety and efficiency of EUS-HGS and EUS-AG in patients with unreachable papillae using a prospective, multicentre, randomised, controlled trial.

## Methods/design

### Ethical statements

The study was approved by the Medical Scientific Research and New Technology Ethics Committee of Shengjing Hospital of China Medical University (approval number: 2018PS525K) on 22 November 2018. Subsequently, the boards of the two participating hospitals gave permission to conduct the trial. Informed consent will be obtained from each participant or from each of the participant’s legally responsible relative. The trial was registered in the Chinese Clinical Trial Registry (ChiCTR), ChiCTR1900020737, on 15 January 2019.

### Participating centres

The three participating centres, including Shengjing Hospital of China Medical University in China, Qilu Hospital of Shandong University in China, and Institut Paoli Calmettes in France, were selected at the workshop of the International Society of Endoscopic Ultrasound (ISEUS). This selection was based on the fact that a few experts are capable of performing EUS-AG over the world, and the number of EUS-BD procedures is relatively higher at these centres. The background characteristics and procedures of this protocol were approved by all the centres involved.

### Patients

Patient recruitment will be carried out in three centres by gastroenterologists, surgeons, or endoscopists in their own centre who will evaluate the cases in the inpatient wards or in the outpatient consultation areas. After detailed introductions of this trial, patients will be given the opportunity to ask questions and decide whether to participate. The patients will also be reminded that consent is completely voluntary and can be withdrawn at any time. Patients who decide to participate will be randomly assigned (1:1) to receive EUS-HGS or EUS-AG for relief of biliary obstruction. A flowchart of the study design is shown in Fig. 1.

**Fig. 1 Fig1:**
[figure not shown]
A flowchart of the study design

### Inclusion criteria

Patients with unresectable malignant biliary obstruction must meet the following inclusion criteria:
IH bile duct dilation confirmed by ultrasonography or CTFailed ERCPAnatomical abnormalities (congenital malformations, upper digestive tract surgery, or tumour mass)Distal biliary obstruction and pyloric or duodenal obstruction caused by tumoursInformed consent

### Exclusion criteria

Patients with clear contraindications to endoscopy will be excluded:
Haemoglobin level ≤ 8.0 g/dlCoagulopathy (platelet count < 50,000/mm^3^, international normalised ratio > 1.5) or having taken oral anticoagulation agents, such as aspirin or warfarin, in the previous weekSevere cardiorespiratory dysfunctionPsychiatric disease, drug addiction, or other reason for unreliable follow-up or responses to questionnairesOther conditions that negatively affect compliance, which place the patient at increased risk, or otherwise make them unsuitable for participation

### Primary endpoints

The primary endpoint is the efficiency of HGS and AG described by technical success and clinical remission rates. Technical success is defined as successful stent placement which is clarified by endoscopists soon after the operation. Clinical remission will be evaluated 1 month postoperatively as it is defined as a decrease in the serum bilirubin level to less than 75% of preprocedural values within 30 days after stent placement. Only patients with both technical and clinical success are considered to reach the primary endpoint.

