### Data collection

The baseline assessment will be performed after randomisation. Basic information including sex, age, race, and diagnosis will be recorded retrospectively. Concerning feasibility and safety, complete blood counts, hepatic and renal function tests, and biochemical tests will be performed on the day before the operation. Ultrasonography or upper abdominal computed tomography (CT) will be performed before the operation to confirm IH biliary dilation caused by obstruction.

Patients will undergo an examination of their bilirubin levels on days 1 and 3 postoperatively to evaluate the efficiency of the operations. Upper abdominal CT will be performed postoperatively to clarify the position of the stent. Technical success is defined as successful stent placement, and clinical remission is defined as a decrease in the serum bilirubin level to less than 75% of preprocedural values within 30 days after stent placement.

Adverse events at any time will be recorded and classified as post-procedure (up to 14 days) and late (any time after 14 days) and graded according to the American Society for Gastrointestinal Endoscopy lexicon’s severity grading system [16].

Stent patency is described by time to stent dysfunction needing re-intervention. The criteria for stent dysfunction are as follows: (1) cholangitis, (2) 50% increase in bilirubin from the lowest level post-index procedure, (3) 20% increase in bilirubin from the lowest level post-index procedure and evidence of obstruction on imaging, and (4) endoscopic or radiological re-intervention confirming stent blockage or migration.

Additionally, hospitalisation data including the length of hospital stay and total hospitalisation expenses will be recorded. The schedule of enrolment, interventions, and assessments is shown in Fig. 2.

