### Follow-up

The final study follow-up is scheduled at 1 year postoperatively and includes evaluation of perioperative mortality and operative complications. Follow-up assessments of the bilirubin level (total bilirubin, conjugated bilirubin, and unconjugated bilirubin) and survival status are scheduled at 1 month, 3 months, 6 months, and 1 year after the operation or until death. If follow-up information is unable to be obtained, the patient will be considered lost to follow-up, and their data will be documented accordingly.

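### The primary endpoint does not fix which bilirubin reading decides remission, and as worded it credits a fall reached only after re-drainage

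*Protocol article*

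**What the plan says.** All references are to the protocol article.

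- **Primary endpoints.** The endpoint is called efficiency and is a composite: "Only patients with both technical and clinical success are considered to reach the primary endpoint". Technical success is placement of the stent. Clinical remission is "a decrease in the serum bilirubin level to less than 75% of preprocedural values within 30 days after stent placement", and the same sentence says that "Clinical remission will be evaluated 1 month postoperatively".
- **Data collection.** The 30-day definition is repeated. Patients also have an "examination of their bilirubin levels on days 1 and 3 postoperatively to evaluate the efficiency of the operations". Re-intervention appears here only for a secondary endpoint: "Stent patency is described by time to stent dysfunction needing re-intervention".
- **Follow-up.** Bilirubin and "survival status are scheduled at 1 month, 3 months, 6 months, and 1 year after the operation or until death". No window is given for the 1-month visit.
- **Randomisation and interventions.** An antegrade attempt that fails and is converted to hepaticogastrostomy stays in the AG group as a technical failure. The trial is open-label.
- **Statistical analysis.** Missing data are handled by deletion.

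**The concern.** The primary endpoint is a yes/no classification, so its wording should put each patient in one class. Here it leaves three gaps.

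1. **Deciding reading.** A threshold reached at any time within 30 days and a threshold met at the 1-month reading are different rules. They disagree for a patient who responds early and then re-obstructs.
2. **Re-drainage.** Neither component of the composite asks whether the fall was obtained with the index stent alone. A stent that was placed but did not drain can be credited with the effect of a second procedure. The plan already refuses such credit when an AG placement fails and is rescued by HGS.
3. **Early death.** If the 1-month value decides, a patient who dies before it has no value, and the deletion rule removes that patient from the comparison. The Discussion itself stresses the limited lifetime of these patients.

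If the wording stands, the choice between rules could be made once open-label results are known. Stent failures and early deaths could also be counted in ways that flatter one or both arms.

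**Working it through.** **Step 1. Apply the wording to patient types.** In rows A to F the stent was placed, so technical success is met.

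| Patient | Any value within 30 days | 1-month value decides |
|---|---|---|
| A. Below 75% on day 3 and at 1 month, no re-drainage | success | success |
| B. Below 75% on day 3, above it at 1 month, no re-drainage | success | failure |
| C. Above 75% on days 1 and 3, re-drained on day 10, below 75% at 1 month (within 30 days) | success | success |
| D. Below 75% on day 3, re-obstructed and re-drained, below 75% at 1 month | success, earned before re-drainage | success, obtained through re-drainage |
| E. Below 75% on day 3, dies before 1 month | success | no value, deleted |
| F. Above 75% on days 1 and 3, dies before 1 month | no qualifying value | no value, deleted |
| G. AG placement failed, converted to HGS, below 75% at 1 month | failure (technical) | failure (technical) |

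B and E show that the deciding reading matters. C is a success under both rules although the index stent did not work, whereas G is a failure. E and F show the effect of deletion: with s successes among n patients and m deaths deleted as non-evaluable, the rate reported is s/(n − m) instead of s/n, which is higher whenever s and m are above zero.

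The missing visit window adds a smaller gap. A 1-month visit on day 33 would give a value outside the 30-day limit.

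**Step 2. The plan's denominator.** Sample size calculation gives 67 evaluable patients per group and 74 after a 10% allowance. 67 × 1.10 = 73.7, rounded up to 74, which matches.

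**Step 3. How many patients could change class through re-drainage.** The documents give no early re-drainage rate, so 5–10% is an assumption.

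- 0.05 × 67 = 3.35
- 0.10 × 67 = 6.7

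That is about 3–7 patients per group. It is an upper limit, because it treats every re-drained patient as type C: no earlier qualifying fall, then a qualifying fall by day 30.

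**Step 4. What a shift in one arm could do (illustration only).** The plan gives ranges of success rates, not a design pair. Take HGS 93.7% and AG 77%, both quoted in the Discussion, as an assumed pair, with n = 67 per group and two-sided 5%:

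power = Φ{[d√n − 1.96√(2p̄(1 − p̄))] / √[p₁(1 − p₁) + p₂(1 − p₂)]}

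- Base: d = 0.167 and p̄ = 0.8535, so (1.367 − 0.980)/0.486 = 0.796 and power is 0.787.
- Credited re-drainage raises AG alone by 3 points (80%): power 0.653.
- Credited re-drainage raises AG alone by 5 points (82%): power 0.546.
- A stricter reading lowers both arms by 3 or 5 points: power 0.722 or 0.686.

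A shift confined to one arm matters much more than the same shift in both.

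**The case against.** **The timing statements can be reconciled.** Primary endpoints joins the 1-month evaluation and the 30-day window in one sentence, so a fair reading is that status is judged at 1 month because the window then closes. This stands in part: the wording is ambiguous, not contradictory. It still does not settle patient B.

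**Days 1 and 3 are not a rival rule.** A reader might infer a third deciding rule, because Data collection ties those readings to efficiency, which is also the name of the primary endpoint. The documents do not support that. The readings lie inside the 30-day window, the same paragraph repeats the 30-day definition, and nothing names them as deciding remission.

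**Re-drainage is not credited under every conceivable reading.** If only early values counted, patient C would fail. Under the any-value rule, patient D earns success before the second procedure. The problem is confined to technically successful patients whose qualifying value comes after re-drainage.

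**The credit comes from silence.** The full protocol or SAP may deal with intercurrent re-drainage, and the rule on converted AG cases concerns failed placement, not later dysfunction. Both remarks are fair. But the article gives an operative definition of primary success, and that definition, applied as written, yields the result in row C.

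**No differential between arms is shown.** An equal proportional loss of 5–15% in both arms would shrink a 16.7-point contrast only to 15.9–14.2 points (16.7 × 0.95 and 16.7 × 0.85). This stands. The Discussion says that re-intervention is harder after AG than after HGS and names tumour growth as the main cause of re-obstruction of the AG stent. A differential is therefore plausible, but its direction cannot be derived.

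**Conclusion.** The concern holds in a limited form. The wording leaves open whether any qualifying value within 30 days or the 1-month value decides. It also counts as a success a technically successful patient who did not respond to the index stent and whose bilirubin fell only after re-drainage within 30 days. If the 1-month value decides, deletion of missing data would remove patients who die before it.

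The size is unknown. The figure of at most about 3–7 reclassified patients per 67 rests on an assumed 5–10% re-drainage rate, and the power figures rest on an assumed pair of success rates. That pair should not be taken as the design assumption: 93.7% v 77% gives 67 per group only with the unpooled formula (66.5; the pooled formula gives 70), and 89% v 100% also gives 67 with the pooled formula (66.2). The finding depends on none of these numbers. It rests on the classification in Step 1.

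**What to change.** In Primary endpoints:

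- Name one deciding reading and its visit window, for example the 1-month value, and make that window consistent with the 30-day limit.
- Count any further biliary drainage procedure, or death, before a qualifying reading as failure in both arms.
- State that these patients stay in the denominator and are not subject to the deletion rule in Statistical analysis.

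In Data collection, state that the day 1 and day 3 values are descriptive unless they are named as deciding. If the sponsor prefers the any-value rule, list which scheduled readings count and require the qualifying one to precede any re-drainage.

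With the 1-month value as the deciding reading, patient A is a success and B to G are failures. With the any-value rule, A, B, D and E are successes and C, F and G are failures. Either choice gives one class per patient.

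The change concerns how outcomes are counted, not who is re-drained or when. It costs a wording amendment, since the readings are already scheduled, and slightly less favourable success rates. Choosing the 1-month value also makes the endpoint one of sustained response, with some overlap with stent patency. The choice should be fixed before outcome data by arm are examined.

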### Secondary endpoints

The secondary endpoints are as follows:
The overall survival rate for patients undergoing EUS-HGS and EUS-AGStent patency, complication rate, length of hospital stays, and hospitalisation expenses of EUS-HGSStent patency, complication rate, length of hospital stays, and hospitalisation expenses of EUS-AG

### Randomisation and interventions

The randomisation list will be generated by an independent statistician using block randomisation with variable block size (four or six) and kept in sealed envelopes without access by the investigators. Once a patient is enrolled by project secretary, the trial coordinator in Endoscopy Center of Shengjing Hospital of China Medical University will open an envelope and publish the final result of randomisation to all trial participants after confirmation, as this is an open-label design.

The equipment used will include a linear array echoendoscope (EG3830UT; Pentax, Tokyo, Japan) in combination with an ultrasound scanner (EUB 6500; Hitachi, Tokyo, Japan). A 19-G needle (EUS N-19-T; Wilson-Cook Medical, Winston-Salem, NC, USA) will be used for puncture, and a 0.035-in. guidewire (Jagwire; Boston Scientific, Natick, MA, USA) will be used for guidance. A cystotome (6 Fr; Wilson-Cook Medical) will be used to dilate the tract and create a large fistula. A fully covered metallic stent (Wilson-Cook Medical/Boston Scientific) or bare metallic stent (Wilson-Cook Medical/Boston Scientific) will be used for biliary drainage.

The former part of the procedure is the same for both EUS-AG and EUS-HGS. First, the echoendoscope will be advanced into the stomach, and the left lateral lobe liver will be scanned. A dilated IH bile duct close to the gastric wall will be selected as the puncture point. Then, to avoid the blood vessels in the puncture path, the local vasculature will be checked using colour Doppler ultrasonography, and a 19-G ultrasound puncture needle will be advanced into the IH duct. Next, bile aspiration and cholangiography will be performed to further clarify the location of the puncture needle and delineate the dilated biliary tree down to the point of obstruction.

In the AG group, a guidewire will be inserted through the puncture needle and guided into the intestine through the ampulla or anastomosis. A temporary fistula between the stomach (or jejunum in patients with total gastrectomy) and the left hepatic duct will be formed by cystectomy. Once the fistula has been dilated, a self-expandable bare metallic stent measuring 6–8 cm will be deployed into the malignant biliary obstruction in an antegrade fashion.

In the HGS group, a guidewire will be inserted through the needle and placed in the common bile duct. A cystotome will be used to create a fistula, and a fully covered metallic stent will be deployed into the fistula between the stomach (or jejunum in patients with total gastrectomy) and IH bile duct. Sometimes, a bare stent will be placed through the covered stent to avoid stent migration.

Finally, all devices will be removed after confirming with a contrast agent that bile flows well through the stent or stricture. To avoid bile leakage into the peritoneum, a 7-Fr naso-biliary catheter will sometimes be placed through the metallic stent for 48 h. In cases of failed EUS-AG, EUS-HGS will be performed for being recorded as technical failed cases in the EUS-AG group. To ensure data integrity, this group of patients will still be followed up as scheduled and recorded properly.

Both EUS-HGS and EUS-AG are established procedures of biliary drainage; there are no anticipated problems that would be detrimental to our patients. We do not anticipate the need for formal stopping rules for the trial; nevertheless, severe adverse events will be recorded in a timely manner and will be supervised by the monitoring board.

A Consolidated Standards of Reporting Trials (CONSORT) checklist for this study is provided in Additional file 1. The Standard Protocol Items: Recommendations for Interventional Trials (SPIRIT) checklist is provided in Additional file 2.

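### If allocations are published to recruiting teams as well as patients, short blocks of four or six let a recruiter who tracks the results guess about 69% of assignments

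*Protocol article*

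**What the plan says.** All the allocation rules are in the protocol article under Randomisation and interventions.

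- **List.** "The randomisation list will be generated by an independent statistician", with "block randomisation with variable block size (four or six" as the block sizes, and held in sealed envelopes that investigators cannot access. The list is in the singular, and stratification by centre is not mentioned.
- **Opening.** After the project secretary has enrolled the patient, "the trial coordinator in Endoscopy Center of Shengjing Hospital of China Medical University will open an envelope".
- **Disclosure.** The coordinator will then "publish the final result of randomisation to all trial participants after confirmation", and the reason given is "as this is an open-label design".

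Two other sections bear on this. Under Patients: "Patient recruitment will be carried out in three centres by gastroenterologists, surgeons, or endoscopists in their own centre". Under Exclusion criteria, the last item is open-ended and covers conditions that "otherwise make them unsuitable for participation".

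**The concern.** Sealed envelopes and central opening protect the next allocation only if those who decide on enrolment cannot infer it from past ones. With short balanced blocks, past results carry that information: an arm that is behind must catch up within a few patients. An open-label design is a reason to tell the patient and the team doing the procedure. It is not a reason to tell everyone.

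If recruiters at all three centres receive every result, one who keeps a tally has a useful guess about the next assignment before deciding whether to put a patient forward. The last exclusion criterion leaves room for judgement. The Discussion reports that most studies find lower success and lower complication rates with EUS-AG, and that the choice of approach depends on anatomy and stricture location, so a recruiter may well have a view on which patient suits which arm. Selective enrolment of this kind would bear on the comparison of technical and clinical success. Baseline comparisons and covariate adjustment could address measured imbalance but not unmeasured imbalance.

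**Working it through.** **Inputs from the article:** allocation 1:1; blocks of 4 or 6; 148 patients; three centres. **Not given, so assumed:** the mix of block sizes (equally likely, with the extremes shown) and the centres' shares of recruitment. The article gives no predictability figure to reproduce.

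**Step 1. Guessing rule.** Guess the arm with fewer assignments so far, and toss a coin when the arms are level. The recruiter need not know where blocks start, because every completed block returns the difference to zero.

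**Step 2. Exact rate.** For a block of size 2b, expected correct guesses = b + 2^(2b−1)/C(2b, b) − 1/2.

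- Block of 4: 2 + 8/6 − 0.5 = 2.833, and 2.833/4 = 70.8%.
- Block of 6: 3 + 32/20 − 0.5 = 4.1, and 4.1/6 = 68.3%.
- Equal numbers of each: (2.833 + 4.1)/10 = 69.3%.

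Any mix lies between 68.3% and 70.8%.

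**Step 3. Simulation.** Over 4,000 lists of 148 patients with block boundaries unknown to the guesser, the rule was right 69.2% of the time. A Bayes-optimal guesser also scored 69.2%. About 5.5% of assignments could be known with certainty.

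**Step 4. Restricted disclosure, one shared list.** Each centre sees only its own results and uses the same rule. Average correct-guess rate by assumed centre shares:

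| Shares (%) | Correct guesses |
|---|---|
| equal | about 52% |
| 45/35/20 | about 52% |
| 60/30/10 | about 53% |
| 80/10/10 | about 54% |
| 90/5/5 | about 57% |

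**Step 5. Restricted disclosure, separate list per centre.** Each centre then sees the complete sequence of its own list, so Step 2 applies within the centre and the rate stays at about 69%.

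**Step 6. Larger blocks.** The same formula gives 4 + 128/70 − 0.5 = 5.329 for a block of 8 (66.6%) and 5 + 512/252 − 0.5 = 6.532 for a block of 10 (65.3%). Widening the range upwards helps, but only modestly.

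**The case against.** The strongest objection concerns the word 'participants'. The ethics section uses it for patients who give consent, while sites are called participating hospitals, centres or institutions. On that usage the sentence says only that patients learn their allocation, and nothing reaches recruiters. This stands as a real alternative reading, and under it the 69% does not apply if each patient hears only their own result. It does not settle the matter. Publishing a result to all participants is an odd way to describe telling one patient, and the sentence sets no limit on who is told.

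A reader might infer that every allocation certainly reaches every recruiter and that a single unstratified list certainly serves all centres. The article supports neither as fact. The single list is inferred from the singular noun, the single coordinator and the lack of any mention of stratification.

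The safeguards also count: an independent statistician, sealed envelopes, a project secretary who enrols, a central coordinator, and disclosure only after enrolment is confirmed. They hide the list itself, but do not prevent prediction from published results.

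The 69% is an average for someone who tracks every result. By simulation, the arms are level at about 39% of assignments, where the guess is a coin toss. With 148 patients over about 25 months, one allocation comes roughly every five days, so holding a patient back for a better slot would delay drainage. That limits manipulation of timing, but not discretionary exclusion. Recruiters are also not only endoscopists: gastroenterologists and surgeons are listed too.

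**Conclusion.** The point holds conditionally. If the published results reach recruiting teams, which the wording permits but does not establish, allocation is predictable about 69% of the time on average (68.3% to 70.8%; chance is 50%) for a recruiter who follows them. That figure does not depend on whether there is one list or several, provided the recruiter knows which results belong to which list. It rests on the printed block sizes and 1:1 ratio, and on a recruiter who keeps a tally.

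It measures opportunity. Nothing in the article shows that recruiters would act on a guess, and no size of bias in the primary endpoint can be derived from it. The benefit of restricting disclosure, down to roughly 52% to 57%, further assumes one shared list and the illustrative centre shares above. The sentence should be changed because the correction costs almost nothing and removes the doubt about who is told.

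**What to change.** Replace the disclosure sentence with: *the coordinator discloses each allocation only to the enrolling centre's treating team and the patient; results and running tallies are not circulated to other centres or recruiters.* Keep the existing rule that disclosure follows confirmed enrolment.

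State in the same section whether one list serves all centres or each centre has its own. If lists are separate by centre, restricting disclosure is not enough, and a less predictable scheme is needed within centre, for example a wider range of block sizes extending upwards. Step 6 shows that the gain from larger blocks alone is modest. Asking for the present block sizes to be withheld would serve no purpose, since they are already published and the guessing rule does not need the block boundaries.

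The cost is one or two sentences and a shorter distribution list for each notice, with no extra patients or staff and no change to the open-label design. The small downside is that centres lose the running tally. Separate lists would also require a revised list for the patients still to be randomised.
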